### Assessment time points

Measurements and observations are scheduled in all groups in the same manner (Figure 3). An inclusion assessment will be performed at the study entry and is documented in a case report form (CRF). The baseline CRF includes the neurological classification, assessment of injury date and time, medical history, concomitant injury, acute SCI therapy concerning high-dose methylprednisolone treatment as well as surgical intervention.

**Figure 3 F3:**
[figure not shown]
**Longitudinal trial design.** Legend: Assessment points and time frames. The starting point of the time line is the time of injury not the time of surgery. In the case of difficulties in scheduling the visits 2 to 5 may be conducted within the indicated time windows (*italic*). The circadian rhythmics are respected.

At the 5 study visits, equal blood samples and clinical data will be obtained. The clinical data comprise infections, medication, surgery, and blood transfusions. The first assessment should be completed as early as feasible after the injury, preferably before surgery, otherwise at least within 31 hours post-injury. The second assessment point refers to a time window of 31–55 hours post-injury. To ensure a sufficient time interval to the first assessment the second one should be performed on the following day at the earliest. This allows a better intra-individual analysis. The visits 3, 4 and 5 refer to day 7, 14 and to 10 weeks after injury, respectively. Blood withdrawals, except at time point 1 should be performed between 7:00 and 11:00 am. This setting determines the influence of the circadian rhythm to a minimum.

In the case, if it is unavoidable that a patient may be assigned to the study later as 31 hours (delayed recruitment) e.g., due to later admission or transfer to a study center (see also sample size calculation), study inclusion is tolerated at any later time point. In individual cases of delayed recruitment or patient’s absence, documentation of visits 2–5 may be scheduled in extended time windows (Figure 3).

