### Statistical analysis

Data analysis of the primary endpoint consists of a comparison, between the 3 groups at the early and subsequent follow-up assessment points using one-way ANOVA or nonparametric tests, if appropriate. The analysis will be performed using the full dataset comprising all patients included according to the criteria as defined in the study protocol. In addition, in patients with complete intra-individual datasets also changes over time within the groups will be assessed with descriptive methods. Furthermore, in the case of a relevant amount of missing values, multiple imputation will be taken into consideration for verification of the analysis of the original data. Data obtained from patients treated with methylprednisolone will be primarily analyzed in a casuistic manner.

The statistical analysis of the administrative interim evaluation has been performed using SPSS for Macintosh, Version 19.0.

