### Observation period

Observational time points (Figure 2) range from acute to sub-acute stages after SCI comparable to the pilot study [6]. Here, the time schedule corresponded to the hallmarks of parenchymal inflammation following SCI. The implementation of sub-acute assessments is in line with previous trials that demonstrated mid- and long-term alterations of the immune system after SCI [8,18,19].

The setting of defined time corridors instead of time points provides a more complete tracking of the participants. In order to prevent a high amount of missing datasets due to loss to follow-up, the protocol allows an inclusion at each documentation time point.

The administrative interim analysis of data completeness for the main laboratory parameters indicates - depending on the group or visit – a completeness of data between 24% and 91% with critical rates of completeness at visit 1 and visit 5, particularly in the control group (Table 5). As a consequence, the recruiting centers have been requested to enroll the patients as soon as possible after injury. Additionally, we intend to address the challenge of loss to follow up by travelling to external rehabilitation centers or by phone calls to remind patients of their study visit at the outpatient clinic. The rate of complete longitudinal datasets ranges between 18% and 36% but is expected to increase during the further trial course since trial routines are better established. Noteworthy, the sample size calculation takes 50% of missing values into account and was performed for one-way ANOVA. Repeated measure analysis requires lower sample sizes. Therefore, it seems feasible that a relevant amount of complete longitudinal datasets can be achieved also for the description of the intra-individual course of the SCI-IDS. Pursuing this study concept, serial investigations on short- and mid-term changes of the immunological function are provided.

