### Primary outcome measure

For meeting the purpose of a more comprehensive characterization of the SCI-IDS and establishing prognostic surrogate parameters, it is essential to implement specific parameters, readily validated in clinical immunology, robust and reproducible [14]. Quantification of immune cell populations in the blood using FACS is a clinically established and precise method that qualifies as primary outcome measure. Our primary measure is the determination of HLA-DR-molecules per monocyte. Alterations in HLA-DR expression on monocytes occur early enough to identify patients at high risk for relevant immune depression and consecutive development of infections. Significantly decreased monocytic HLA-DR levels have been observed as early as day one after acute cerebral ischemia in patients who developed infectious complications in comparison to patients with an uncomplicated clinical course [27]. Furthermore, the method is already established and available in centralized immunological laboratories. It has sufficient diagnostic specificity as a basis for clinical decision-making and therefore is clinically highly relevant. Moreover, we implemented a large setting of secondary endpoints for the development of very early predictive parameters, for example on the level of mRNA expression.

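### Early visits are wide corridors compared by nominal visit without hours since injury, and the next-day rule does not secure the visit 1–2 interval it promises

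*Protocol article*

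**What the plan says.** Under Assessment time points, time runs from injury. For visit 1: "The first assessment should be completed as early as feasible after the injury, preferably before surgery, otherwise at least within 31 hours post-injury". For visit 2: "The second assessment point refers to a time window of 31–55 hours post-injury". The two are linked by one spacing rule: "To ensure a sufficient time interval to the first assessment the second one should be performed on the following day at the earliest". Its stated benefit follows: "This allows a better intra-individual analysis". Blood is drawn between 07:00 and 11:00 at every visit except the first. All groups follow the same schedule, and the baseline case report form includes "assessment of injury date and time".

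The Discussion (Observation period) presents the corridors as a deliberate choice: "The setting of defined time corridors instead of time points provides a more complete tracking of the participants".

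The Statistical analysis section describes a "comparison, between the 3 groups at the early and subsequent follow-up assessment points" by one-way ANOVA or, where appropriate, a nonparametric test. Change over time within groups is described only, in patients with complete data. Elapsed time since injury enters neither analysis.

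**The concern.** Two things do not fit together.

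- **The spacing rule.** It is meant to guarantee an adequate gap between the first two samples, but it counts calendar days. Visit 1 has no clock-time limit, so a sample late one evening and another early the next morning comply. Another patient may have samples two days apart. The same underlying hourly change then appears as very different visit 1–2 changes.
- **The group comparison.** Everyone inside a corridor is treated as sampled at the same time. The groups are defined by injury, not randomised, so nothing in the design balances sampling hours between them. If HLA-DR is changing over these hours, the spread adds noise. If one group is sampled systematically later, timing is also mixed with the lesion effect.

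At stake are the early group comparisons and the earliest within-patient measure in the study.

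**Working it through.** **1. Permitted visit 1–2 interval** (inputs from Assessment time points: visit 1 at 0–31 h at any clock time; visit 2 at 31–55 h, drawn 07:00–11:00, on a later calendar day).

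- Minimum: visit 1 just before midnight and visit 2 at 07:00 give a limit of 7 h. Example: injury at 00:00, visit 1 at 23:50 (23.8 h), visit 2 at 07:00 the next day (31 h); interval 7.2 h.
- Maximum: injury at 00:40, visit 1 at that moment, visit 2 at 07:40 two days later; interval 55 h. This end is theoretical. If visit 1 is assumed to come no earlier than 3, 6 or 12 h after injury, the maximum is 52, 49 or 43 h; the minimum stays about 7 h.
- Between the ends: weighting every permitted combination equally (an assumption, not a forecast), the median is 28 h, the 5th–95th percentile range 12–47 h, 4% of intervals are under 12 h and 35% under 24 h.

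**2. The plan's own sample size** (Sample size calculation: effect size 0.18, two-sided alpha 0.05, type II error 0.2, 56 evaluable, groups 48/31/39).

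Reading 0.18 as variance of group means over within-group variance, the noncentrality is 56 × 0.18 = 10.08 on 2 and 53 degrees of freedom. Power is 0.795 at 56 patients and 0.803 at 57, so the stated 56 is reproduced to within one patient. This design serves as the yardstick below; the article places the primary endpoint at day 3–4.

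**3. Cost when timing is alike in all groups.**

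Assume a slope of b SD per 24 h and draw times uniform over a corridor of W hours. Within-group variance becomes s² = 1 + (b·W/24)²/12, and the effect becomes 0.18/s². The slopes are assumed, because the article gives none.

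| b (SD per 24 h) | s², visit 2 (W = 24) | Power at 56, visit 2 | s², visit 1 (W = 31) | Power at 56, visit 1 |
|---|---|---|---|---|
| 0.25 | 1.005 | 0.793 | 1.009 | 0.791 |
| 0.5 | 1.021 | 0.786 | 1.035 | 0.780 |
| 1.0 | 1.083 | 0.760 | 1.139 | 0.738 |

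The type I error stays at 0.05 throughout.

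**4. What a timing difference would do, if there were one.**

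Let controls be sampled h hours away from both SCI groups on average, with no lesion effect. With the control share w = 39/118 = 0.331, the spurious effect is w(1−w)(b·h/24)²/s². For b = 0.5 and h = 6 in the visit 2 corridor this is 0.221 × 0.125²/1.021 = 0.0034.

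| b (SD per 24 h) | Type I error at 56, h = 6 | Type I error at 56, h = 12 |
|---|---|---|
| 0.25 | 0.053 | 0.064 |
| 0.5 | 0.064 | 0.108 |
| 1.0 | 0.104 | 0.293 |

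Both h and b are assumptions.

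**5. Is such a difference likely at visit 2?**

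The corridor is 24 h wide and opens at the clock time of injury plus 7 h. It straddles two morning blocks only when the injury falls between 00:00 and 04:00. For the other 20/24 = 83% of injury clock times, visit 2 lies in a single 4-hour block. Hours since injury at visit 2 therefore depend mainly on the clock time of injury, and late transfer can move them little. Visit 1 has no such constraint.

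**The case against.** The strongest reply is that no group bias has been shown, and that stands. A reader might infer that late transfer of SCI patients makes them look more immune-depressed, or that the false-positive rate approaches 30%. The article does not support either inference:

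- It reports no sampling hours by group and no rate of HLA-DR decline. The early finding it cites, "Significantly decreased monocytic HLA-DR levels have been observed as early as day one", compares stroke patients with and without infectious complications. It is a difference between patients in another disease, not a slope.
- The morning-draw rule leaves little room for a 6–12 h group shift at visit 2.
- In Table 5, visit 1 completeness is 61% (T4 and above), 55% (T5 and below) and 53% (controls), which does not suggest that SCI patients arrive later than controls.
- All groups share one schedule anchored at injury.

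Four further points are fair. Without the next-day rule the interval could be close to zero, so the rule does help, and its claim of a better intra-individual analysis is true as a comparison. Both ends of the 7–55 h range are edge cases. The within-patient analysis is only descriptive. The corridors are an openly reasoned trade-off for completeness.

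It can also be said that covariates belong in an analysis plan that is not shown. That holds for detail, but the article names its test, and a one-way ANOVA has no place for elapsed time. Adjustment would change a stated method rather than fill in an omitted one. Nor does the rule's usefulness make the interval sufficient: improving on zero does not set a minimum in hours.

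**Conclusion.** The point holds in a limited form. The next-day rule fixes no minimum in hours and allows roughly 7 h to a theoretical 55 h, so it does not deliver the assurance attached to it, and visit 1–2 changes are not comparable between patients on a common time scale. This follows from the stated rules alone.

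The group comparisons ignore hours since injury although injury date and time are recorded. With similar timing across groups, the visit 2 corridor lowers power from 0.795 to 0.760–0.793, assuming slopes of 0.25–1.0 SD per 24 h and uniform draw times. That is a modest loss.

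Confounding of the lesion effect by sampling time is a possibility to check, chiefly at visit 1, not a demonstrated fault. The 0.293 type I error is the worst corner of an assumed grid and should not be read as the trial's error rate. Corridor width is established only for visits 1 and 2. The extended limits for visits 2–5 are in Figure 3, which was not available, so nothing is claimed about them. The change is worth making because it is cheap and the marker is studied for its early course.

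**What to change.** 1. Compute hours from injury to blood draw for every sample. Injury time is on the baseline form; confirm that draw time is recorded too.
2. Tabulate these hours by group and visit, so that any imbalance is visible.
3. Include hours since injury as a covariate (linear, or a spline with two degrees of freedom) in the visit 1 and visit 2 group comparisons, at least as a prespecified sensitivity analysis.
4. Use actual hours rather than visit number as the time axis for the descriptive within-patient change.
5. Drop or qualify the statement that sampling on the next day ensures a sufficient interval.

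The cost is one or two degrees of freedom and a little more analysis work. Recruitment and the visit schedule do not change.

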### Definition of infections

The most prevalent infections after SCI, in detail chest infections and urinary tract infections, are diagnosed and documented in the study according to established definitions of disease to ensure a biometric comparability [15,21,22] (Table 2). Additionally, a distinction is made between non-symptomatic and symptomatic urinary tract infections, i.e. the latter are classified with regard to evidence of fever, increased spasticity, bladder spasm, suprapubic or flank pain, autonomic hyperreflexia, malaise, or lethargy. All other infections are documented according to the usual diagnostic criteria of the participating centers.

**Table 2 T2:** Diagnostic criteria for chest infection and urinary tract infection

**Type of infection**	**Criteria**
Chest infection, if ≥ 3 criteria apply	Temperature < 36.0°C or ≥ 37.5°C
	Putrid secretion
	Pathological respiration (rales, bronchial breathing, tachypnea > 22/min)
	Opacities in chest x ray (required for the diagnosis of pneumonia)
	Detection of pathogenic germs in sputum
	pO2 < 70 mmHg/O2 saturation < 93%
Urinary tract infection, if ≥ 1 criteria apply	Bacteriuria with bacterial count > 10^5^ cells/ml
	Leukocyturia ≥ 100 WBC/mm^3^, respectively 100.000 WBC/ml
Symptomatic urinary tract infection, if ≥ 1 criteria apply	≥ 1 criteria for urinary tract infection
	≥ 1 of the following criteria: fever, suprapubic or flank discomfort, bladder spasm, increased spasticity, worsening dysreflexia

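### Table 2 calls a urinary tract infection symptomatic when only one of two criteria is met, which contradicts the text above it and leaves no non-symptomatic class

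*Protocol article*

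**What the plan says.** The Protocol article defines infections for the study under Definition of infections, in a paragraph and in Table 2.

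The paragraph states that "a distinction is made between non-symptomatic and symptomatic urinary tract infections", and says of the symptomatic ones that "the latter are classified with regard to evidence of fever, increased spasticity, bladder spasm, suprapubic or flank pain, autonomic hyperreflexia, malaise, or lethargy". There are thus two classes of UTI, and symptoms separate them.

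Table 2 has two blocks on UTI:

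- Any UTI carries the label "Urinary tract infection, if ≥ 1 criteria apply". Its rows are "Bacteriuria with bacterial count > 10^5^ cells/ml" and "Leukocyturia ≥ 100 WBC/mm^3^, respectively 100.000 WBC/ml".
- Symptomatic UTI carries the label "Symptomatic urinary tract infection, if ≥ 1 criteria apply". Its rows are "≥ 1 criteria for urinary tract infection" and "≥ 1 of the following criteria: fever, suprapubic or flank discomfort, bladder spasm, increased spasticity, worsening dysreflexia".

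The Discussion, under Clinical observations, returns only to the general UTI definition by bacterial or white cell count. Nothing elsewhere in the article corrects the label on the symptomatic block.

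**The concern.** The count in a block label governs the rows beneath it. If one of the two rows is enough for symptomatic UTI, two things follow.

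- The first row qualifies alone, and that row is simply the definition of any UTI. The symptomatic class then takes in every UTI, and the non-symptomatic class is empty by construction.
- The second row qualifies alone. A patient with fever from another source and normal urine would be a symptomatic UTI while failing the definition of UTI one block higher.

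A class that the paragraph describes as part of UTI therefore becomes wider than UTI itself.

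At stake is whether this class is coded the same way everywhere. Enrolment and eligibility criteria names seven study centres, and the Discussion treats the determination of infections as crucial. Someone who follows the table and someone who follows the paragraph would code the same patient differently.

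**Working it through.** The plan gives no figure to reproduce. The check is one of logic.

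**Inputs** (all from Definition of infections): two urine findings and five symptoms in Table 2, each present or absent. Let U mean at least one urine finding and S at least one listed symptom.

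**Counts of patterns**

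- All patterns: 2^2 × 2^5 = 4 × 32 = 128
- U, that is any UTI: (4 − 1) × 32 = 96
- U and S: 3 × (32 − 1) = 93
- U without S: 3 × 1 = 3
- S without U: 1 × 31 = 31
- Neither: 1
- Check: 93 + 3 + 31 + 1 = 128

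**Classification under the two readings**

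| Pattern | Count | Table 2 as labelled (one row suffices) | Both rows required (as the paragraph implies) |
|---|---|---|---|
| Urine finding and symptom | 93 | symptomatic UTI | symptomatic UTI |
| Urine finding only | 3 | symptomatic UTI | non-symptomatic UTI |
| Symptom only | 31 | symptomatic UTI | not a UTI |
| Neither | 1 | not a UTI | not a UTI |

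As labelled, 93 + 3 + 31 = 127 patterns are symptomatic UTI. All 96 UTI patterns are among them, so 96 − 96 = 0 are left for the non-symptomatic class. With both rows required, 93 are symptomatic and 96 − 93 = 3 are non-symptomatic. The 31 symptom-only patterns drop out.

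These counts show what the rule does. They say nothing about how often each pattern occurs in patients.

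**Symptom lists.** The paragraph has seven entries and the table five. Pain against discomfort, and hyperreflexia against dysreflexia, can be read as variants of the same items. Malaise and lethargy have no counterpart in the table. So even with both rows required, a UTI with malaise or lethargy as its only symptom is symptomatic by the paragraph and non-symptomatic by the table.

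**The case against.** **The intended rule is plain.** The paragraph makes symptomatic UTI a UTI with symptoms. Each row of the symptomatic block already carries its own count, and the first row has no purpose unless it is joined to the second. The label repeats the one on the block above and looks like a drafting slip. This stands as to cause: it is an inconsistency, not a chosen design. It does not remove the point, because the article prints the label as a working rule and corrects it nowhere. The mismatch in symptoms also survives under the intended reading.

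**Little depends on the class.** Chest infection, pneumonia and overall UTI have their own criteria, which the label does not touch. The primary endpoint is monocytic HLA-DR, and the Statistical analysis section names no analysis of symptomatic UTI. This stands, and it sets the severity.

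**No misclassification is shown.** The case report form is not available. It may already require both elements, or may record only a diagnosis. This stands too.

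A reader might infer that the non-symptomatic class must be large, because the Discussion reports that up to 75% of certain samples carry bacteria. That figure concerns asymptomatic men under intermittent catheterization at a threshold of 10^2 per ml. The study uses 10^5 per ml, which is 10^5 / 10^2 = 1,000 times higher, so the figure does not size the class here.

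A reader might also infer that the error falls more heavily on spinal cord injury patients than on controls. The article gives no rates of urine findings or symptoms by group, so that rests on assumption.

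**Conclusion.** The point holds as an internal contradiction. Read literally, Table 2 leaves no non-symptomatic UTI and counts symptoms without urine findings as symptomatic UTI. The paragraph above it says otherwise, and the two symptom lists differ by malaise and lethargy.

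The reach is limited to the symptomatic/non-symptomatic split. Overall UTI, chest infection, the HLA-DR primary endpoint and the sample size are unaffected. Since the article aims to identify patients at risk of infection, a reader might infer that the data linking HLA-DR to infection are misclassified as a whole. The documents do not support that: the other infection definitions stand on their own, and no stated analysis uses this subclass.

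Severity is minor to moderate, for a secondary clinical classification. The logical result assumes only that the label means what it says. Any effect on recorded data further assumes that a site or programmer applied the label rather than the paragraph, which the article does not show.

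**What to change.** 1. Reconcile the label of the symptomatic block in Table 2 with the paragraph, so that the study classification needs a UTI criterion together with a symptom.
2. Reconcile the two symptom lists into one, used in both text and table. Whether malaise and lethargy belong is for the sponsor to decide and state.
3. Check that the case report form and its instructions use the reconciled definition.
4. Where urine findings and symptoms were recorded separately, re-derive the class for patients already enrolled (64 by April 2013, according to the Discussion under Eligibility criteria). Where only a diagnosis was recorded, say so and report which definition the sites applied.

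Steps 1 and 2 cost a short text edit. Step 3 is a document check. The cost of step 4 depends on what the case report form holds, which is not shown. Neither the sample size nor the primary analysis changes.
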